### Randomisation

Randomisation will be computer-generated by an off-site statistician. The unit of a cluster will be Union Councils. A union council forms the second-tier of local government and fifth administrative division in Pakistan, The Union Councils will be randomly allocated to one of the two arms; arm-1 is the intervention group receiving LTP Plus and TF-CBT whereas Arm-2 is routine care.

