### Study site and population

Participants will be recruited from community settings (e.g. primary care) in Peshawar and Karachi with the assistance of community health workers (CHWs). Karachi is the capital of the province of Sindh, and the largest city in Pakistan, the world's third most populated city (Karachi Metropolitan Corporation). Karachi is a metropolitan city with diverse populations of political and economic migrants, refugees from different religious, linguistic, provincial and national origins who move to settle permanently. Peshawar is the capital of the province KPK, situated close to the border of Afghanistan. It has gone through major changes as a result of the Soviet-Afghan war and ongoing conflicts.

The parents with children aged between 3 and 6 years old will be screened with the Impact of Event Scale-Revised (IES-R) 22-item scale (Sundin and Horowitz, 2002). Those scoring 24 or above will be eligible for a full assessment of PTSD measured by Clinician-Administered PTSD Scale-5 (CAPS-5). The IES-R has been successfully used in Pakistan (Latif *et al*., 2020).

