### Sample size

To have an effect size of 0.45, assuming 5% significance level, 80% power and 10% drop out (Husain *et al*., 2017b) during the study, we need to recruit 300 parents. The objective for which the larger sample size is needed relates to the intra-cluster correlation coefficient (ICC), which measures the degree of similarity in outcome amongst parents in the same cluster; for this, the key is the number of clusters (Rutterford *et al*., 2015). Moreover, groups (and hence clusters) of size around 10 is the optimal size for interventions such as LTP Plus TF-CBT (Biggs *et al*., 2020). We propose a minimum of 15 clusters in each of the LTP + TF-CBT and routine care arms, in order to be able to obtain a relatively precise estimate of the ICC and to check whether it might be greater in the LTP + TF-CBT and routine care arms as the former may have additional variation due to the delivery of the group-based therapy. We, therefore, expect to recruit around 300 parents (approximately 10 each from 15 LTP + TF-CBT and 15 TAU clusters) which will enable the estimation of recruitment and retention rates with sufficiently good precision to inform a full effectiveness trial.

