#### Secondary outcomes

Patient Health Questionnaire (PHQ-9) (Kroenke *et al*., 2001) to assess depression. The scale has been translated into Urdu and validated in Pakistan (Ahmad *et al*., 2018). The Urdu version has been used in previous trials in Pakistan (Husain *et al*., 2017b, 2020). The Cronbach's alpha for the PHQ-9 was reported to be 0.91 and the split-half reliability was 0.77 (Ahmad *et al*., 2018).

Generalised Anxiety Disorder Scale (GAD-7) (Spitzer *et al*., 2006) to assess anxiety. The scale has been translated into Urdu and validated in Pakistan (Ahmad *et al*., 2017). The Urdu version has been used in previous trials in Pakistan (Husain *et al*., 2017b, 2020). The Cronbach's alpha for the GAD-7 was reported to be 0.92 and split-half reliability was 0.82 (Ahmad *et al*., 2017).

Client Service Receipt Inventory (CSRI) (Beecham and Knapp, 2001) will be used to collect information about the use of other health services (including the informal sector faith healers/Imams). The CSRI has been used in a previous trial in Pakistan (Husain *et al*., 2014a).

Ages and Stages Questionnaire (ASQ-3) (Squires *et al*., 2009) to assess physical, social, emotional and cognitive development of children.

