### Statistical analysis plan

The study will be carried out in accordance with the CONSORT guidelines. All analyses will be based on the intention-to-treat sample and missing data will be imputed with multiple imputation procedures as implemented in Statistical Package for Social Sciences (SPSS) software (version 27). To assess the primary and secondary outcomes, a two-sided significance level of 0.05 will be employed to enable the detection of a difference between interventions in both directions. Demographics and baseline variables in the two study arms will be compared using various descriptive statistics of means, standard deviations, and proportions. For primary outcome analysis, a two-sample two-sided test of proportions will be used to compare the difference in the rate of PTSD (assessed using the CAPS-5) at 4-month post-randomisation between LTP Plus and TF-CBT and TAU groups. For the secondary analyses, we will compare the proportions similarly for binary outcomes and use tests for comparing means for the continuous outcome. Additionally, we shall use multivariable techniques in assessing the effect of various covariates including baseline measures on outcomes. If required appropriate transformation of continuous variables will be considered. ICC will be calculated to help future cluster-based research on this topic.

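### The stated between-arm test for ASQ-3, if analysed as a score, is an unadjusted comparison of means, which gives up precision that baseline ASQ-3 and child age could supply

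*Protocol article*

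**What the plan says.** The protocol article lists ASQ-3 under Secondary outcomes, "to assess physical, social, emotional and cognitive development of children". It does not say which ASQ-3 score is used. The Abstract has ASQ-3 taken at baseline and at month 4.

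On child age, Study site and population says "The parents with children aged between 3 and 6 years old will be screened", and the Inclusion criteria repeat that range.

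The Statistical analysis plan gives two routes for secondary outcomes. For binary ones, "we will compare the proportions similarly for binary outcomes"; for continuous ones, the trial will "use tests for comparing means for the continuous outcome". The next sentence says that, in addition, "we shall use multivariable techniques in assessing the effect of various covariates including baseline measures on outcomes". Child age is not named anywhere in the analysis text. Under Randomisation, "The Union Councils will be randomly allocated to one of the two arms"; no balancing on child age is described.

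**The concern.** Children from 3 to 6 years differ widely in development. The protocol's own Table 1 builds its curriculum around half-year bands at ages 3, 4 and 5. If the ASQ-3 score analysed varies with age, or if a child's baseline score predicts the follow-up score, an unadjusted difference in means leaves that predictable variation in the error term. The comparison is then less sensitive than the data allow.

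Child development is half of the intervention's rationale and ASQ-3 is its only measure. A pilot that looks for indications of effect gains from the narrowest interval its data can give, and both covariates are available at almost no cost.

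**Working it through.** **Inputs from the protocol article.** 300 parents in 15 + 15 clusters of about 10, so 150 per arm; 10% dropout leaves 150 × 0.90 = 135 per arm, or 135/15 = 9 per cluster. For the test, "a two-sided significance level of 0.05 will be employed". The design power is 80%.

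**The plan's own figure.** Sample size states: "To have an effect size of 0.45, assuming 5% significance level, 80% power and 10% drop out". For a difference in means, n per arm = 2 × (1.960 + 0.842)² / 0.45² = 77.5, rounded up to 78. That is 156 in total, and 156/0.90 gives 174. The stated 300 is not reached this way. An intra-cluster correlation (ICC) of 0.08 with 10 per cluster gives 156 × 1.72 = 269 and 269/0.90 = 299, but no ICC is stated. The layout 30 × 10 = 300 is consistent. Nothing below depends on how 300 was reached, only on 135 analysed per arm.

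**Assumptions not in the documents.** The correlation r between ASQ-3 score and child age, taken as 0 to 0.7; r = 0 stands for a score that is already age-referenced. Where clustering is included, ICC 0.08, with adjustment reducing variance in the same proportion within and between clusters.

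**Gain from age alone.** Adjustment removes a share r² of the variance. Detectable difference in SD units = 2.802 × √[(2/135) × D × (1 − r²)], where D = 1 without clustering and D = 1 + 8 × 0.08 = 1.64 with it. Since √(2/135) = 0.1217, the unadjusted value is 2.802 × 0.1217 = 0.341 for D = 1, and 0.341 × √1.64 = 0.437 for D = 1.64.

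| r | variance removed | detectable, no clustering | detectable, ICC 0.08 |
|---|---|---|---|
| 0 | 0% | 0.341 | 0.437 |
| 0.3 | 9% | 0.325 | 0.417 |
| 0.5 | 25% | 0.295 | 0.378 |
| 0.7 | 49% | 0.244 | 0.312 |

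**Gain from baseline ASQ-3, and from both.** Simulation of 4,000 trials with no effect and no clustering, 135 per arm, age uniform over 3 to 6 years, and an assumed baseline-to-follow-up correlation of 0.5 given age. Mean standard errors in SD units:

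| r | unadjusted | age | baseline | both |
|---|---|---|---|---|
| 0.3 | 0.1217 | 0.1163 | 0.1022 | 0.1009 |
| 0.5 | 0.1217 | 0.1056 | 0.0951 | 0.0915 |
| 0.7 | 0.1218 | 0.0871 | 0.0812 | 0.0755 |

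At r = 0.5, baseline alone cuts the standard error by 1 − 0.0951/0.1217 = 22%, and both together by 1 − 0.0915/0.1217 = 25%. Age on top of baseline adds 1 − 0.0915/0.0951 = 4%. At r = 0, baseline still helps: 0.341 × √(1 − 0.5²) = 0.295 SD.

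**Is there bias?** The age SD is 3/√12 = 0.87 years, or 10.4 months. The chance difference in mean age between arms, with age not clustered, therefore has a standard error of 10.4 × 0.1217 = 1.26 months, with a 95% limit of 2.5 months. At that limit it moves the unadjusted ASQ-3 difference by 1.96 × 0.1217 × r = 0.07, 0.12 or 0.17 SD for r = 0.3, 0.5 or 0.7. The unadjusted standard error already contains this variation: in the simulation the unadjusted test rejected in 5.2%, 4.4% and 4.5% of null trials, against a nominal 5%.

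**The case against.** **The document does not say that ASQ-3 is compared as a mean.** This stands. No score form is given, and a pass/fail version would take the binary route. The point therefore holds only if ASQ-3 is analysed as a score.

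**Age dependence is not established.** This also stands. Table 1 describes the intervention curriculum, not ASQ-3 scoring. If the score is age-referenced, r is near 0 and age brings nothing. Baseline adjustment does not depend on that premise.

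**The multivariable sentence may already cover this.** It stands in part. Its covariate list is open, includes baseline measures and does not exclude child age, so a reader should not infer that the trial ignores these variables altogether. But the analysis is introduced as additional and is aimed at covariate effects, so the stated between-arm comparison remains the unadjusted one.

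**Covariate lists belong in a full analysis plan.** True of the list. The form of the comparison, however, is fixed here.

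Two stronger readings are tempting. One is that a chance age imbalance would bias the result or pass for a treatment effect. Under randomisation it costs precision and, as shown above for unclustered data, does not inflate false positives. Health workers approaching parents in both kinds of cluster might shift child age systematically, but nothing in the document shows that it would. The other is that one child could be counted twice, or different siblings assessed at the two visits. The article does not say this will happen, and a rule for choosing the index child is detail that a condensed article may leave to the full protocol.

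**Conclusion.** The point holds as a matter of efficiency. The stated comparison for continuous secondary outcomes is unadjusted, and for ASQ-3 analysed as a score two useful covariates are at hand. With 135 per arm and no clustering, age alone lowers the detectable difference from 0.34 SD to between 0.34 (r = 0) and 0.24 SD (r = 0.7). With ICC 0.08 the range is 0.44 to 0.31 SD. Baseline ASQ-3 is the more dependable gain: about 22% off the standard error at r = 0.5, under the assumed baseline-to-follow-up correlation of 0.5 given age. All these correlations are assumptions. ASQ-3 is one of four secondary measures in a pilot, so this is a cheap improvement and not an error that threatens the trial.

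**What to change.** State which ASQ-3 score is analysed. If it is a continuous score, replace the unadjusted test of means as the main between-arm comparison with a regression of the 4-month score on arm, baseline ASQ-3 and child age in months, accounting for Union Council clusters (for example a random intercept per Union Council, with a small-sample correction for 30 clusters). If an age-referenced score is used, the age term can be dropped and baseline ASQ-3 kept. The cluster term is needed in any case, because covariate adjustment alone would still treat parents within a Union Council as independent.

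The cost is a few lines in the analysis section. ASQ-3 at baseline is already planned and child age is already needed for eligibility; the baseline form only has to record that age in months. Two individual-level covariates use up little information with about 270 analysed.

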#### Qualitative component

In-depth digitally recorded interviews with participants and focus groups with key stakeholders will complement the quantitative data (Ritchie *et al*., 2013). This is to draw out complex issues that quantitative methods may overlook and to explore possible mechanisms of change in parents. Qualitative evaluation will include narrative experiences of health care providers, school teachers and other stakeholders (CHWs) in the project. Focus Groups will also be held separately with the participants (parents) and other family members, at the end of participation to explore perceived barriers and facilitators to the successful delivery of the intervention and optimise a framework for subsequent implementation at a national level. Separate topic guides will be developed to be used in focus group and interviews with participants and other stakeholders.

All the qualitative interviews and focus group discussions will be digitally recorded and transcribed verbatim. The transcripts will be translated into English. Initial 3–4 transcripts in English will be back translated into Urdu to ensure accuracy. Data will be coded using NVivo software. The process of analysis will be iterative as data collection will progress, using the principles of constant comparison, until category saturation will be achieved. Framework analysis will be conducted to analyse and interpret the qualitative data (Kiernan and Hill, 2018).

To maintain the credibility and trustworthiness of the data and subsequent findings, the researchers will be supervised by experienced researchers with expertise in qualitative methods (ZZ, TK). Sample of the transcripts will be discussed in regular meetings. Engagement in discussion and regular reviews by all researchers will help to ensure the fit of the data to the final analysis and help to minimise bias. Team members will agree the final theoretical framework and key themes and interpretations.

### Summary and implications

There are limited data available from RCTs to guide treatment choices for clinicians in Pakistan caring for patients, particularly parents with PTSD. As a result, there is a need to test low-cost, culturally sensitive, psychosocial interventions (LTP Plus) for parental PTSD in Pakistan. This study is particularly relevant to the achievement of the Sustainable Development Goals (SDGs) such as Health and Wellbeing (Goal 3), gender equality and empowering women (Goal 5), reducing inequalities (Goal 10) and reducing poverty (Goal 1) (Nations, 2016). The proposed study is an important extension of more than 20 years of work looking at the aetiology (Husain *et al*., 2007) and treatment of depression and anxiety in Pakistan (Husain *et al*., 2014b, 2017b, 2020), including a cultural adaptation of interventions (Naeem *et al*., 2015). In Pakistan, a parenting programme (Learning through Play-LTP) was tested for the first time through a cluster randomised study in a rural area of Rawalpindi, Pakistan (Rahman *et al*., 2009) Results indicated that the intervention group had a significantly higher increase in questionnaire scores of maternal knowledge about infant development than the control group at 3 months postpartum (with women in the intervention group answering correctly 4.3 [95% confidence interval (CI) 3.7–14.9, *p* < 0.001] more questions than the control group) but there were no difference in SRQ-20 (distress) scores between intervention and control groups (Rahman *et al*., 2009). A combination of a parenting programme (LTP) and Cognitive Behaviour Therapy was later tested with depressed mothers (Husain *et al*., 2017b, 2020). For both trials, at 3 months, there was a significant reduction in depression scores of mothers in the LTP Plus group compared to the control group. Since research supporting low-cost interventions is scarce, this trial would help build an understanding of the acceptability, feasibility and effectiveness of a low-cost parenting intervention and how it can help support parents experiencing trauma in Pakistan.

Supporting trauma survivor parents through stress reduction and management, parenting education and connecting them with others via group interventions can help them to positively impact the developmental trajectories of their children (Rosenblum *et al*., 2017). Such interventions are particularly important in Pakistan where women and children are the most vulnerable population because of fragile health systems and natural disasters (Jafar *et al*., 2013). A process evaluation nested in a pilot RCT from Pakistan highlighted that it is challenging for women to access facility-based mental health interventions (Rahman *et al*., 2016) therefore a community-based approach involving CHWs can be adopted to improve access to care (Chiumento *et al*., 2017).
